### **Serious Adverse Events (SAEs)**

A Serious Adverse Event (SAE) is defined by the International Conference on Harmonization (ICH) guidelines and GCP guidelines as any AE fulfilling at least one of the following criteria:

- Results in deaths.
- Life-threatening – defined as an event in which the subject was, in the judgment of the Investigator, at risk of death at the time of the event;
- Requiring subject's hospitalization or prolongation of existing hospitalization
- Resulting in persistent or significant disability or incapacity (i.e., a substantial disruption of a person's ability to conduct normal life functions).
- Congenital anomaly or birth defect.
- Optional: Is medically significant or requires intervention to prevent at least one of the outcomes listed above

Life threatening refers to an event in which the subject was at risk of death at the time of the event. It does not refer to an event that hypothetically might have caused death if it were more severe.

Important medical events that may not immediately result in death, be life-threatening, or require hospitalization may be considered as SAEs (optional!) when, based upon appropriate

medical judgment, they may jeopardize the subject and may require medical or surgical intervention to prevent one of the outcomes listed in the definitions above. This means an individual case decision.

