### 9.1.3 Hospitalization – Prolongation of existing hospitalization

Hospitalization is defined as an overnight stay in a hospital unit and/or emergency room.

An additional overnight stay defines a prolongation of existing hospitalization.

The following is not considered an SAE and should be reported as an AE only:

- Treatment on an emergency or outsubject basis for an event not fulfilling the definition of seriousness given above and not resulting in hospitalization.

The following reasons for hospitalizations are not considered AEs, and therefore not SAEs:

- Hospitalizations for cosmetic elective surgery, social and/or convenience reasons.
- Elective treatment of a pre-existing disease or medical condition that did not worsen, e.g., hospitalization for chemotherapy for cancer, elective hip replacement for arthritis.

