### 9.1.5 Suspected unexpected serious adverse reactions (SUSARs)

SUSARs are all serious adverse reactions with **suspected** causal relationship to the study drug that is **unexpected** (not previously described in the Summary of Product Characteristics or Investigator's brochure) and serious. SUSARs will be reported within 24hours.

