## **10. FOLLOW-UP**

### **Follow-up of study participants including follow-up of adverse events**

Patients will be at the hospital at least two days after surgery (surgery = day 1). During this time patients will be asked for any adverse events on a daily basis. Additionally, patients will be followed up one week after surgery for wound inspection and stitch removal. At this follow-up visit patients will be asked for adverse events as well.

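### The SAE definition says any one listed criterion is enough, but labels the medically significant criterion optional, so an important event may be left non-serious

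*Protocol*

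**What the plan says.** In the protocol's section on Serious Adverse Events, the opening sentence makes any single criterion sufficient: "A Serious Adverse Event (SAE) is defined by the International Conference on Harmonization (ICH) guidelines and GCP guidelines as any AE fulfilling at least one". Six criteria follow:

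1. death
2. threat to life
3. hospitalization or its prolongation
4. persistent or significant disability
5. congenital anomaly
6. "Optional: Is medically significant or requires intervention to prevent at least one of the outcomes listed above"

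A later paragraph in the same section takes up important medical events that need not be fatal, threaten life or lead to admission, and says that they "may be considered as SAEs (optional!) when, based upon appropriate"; the condition attached is a clinical view that the patient is in danger and could need treatment. It closes with "This means an individual case decision".

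Section 9.1.3 adds that "An additional overnight stay defines a prolongation of existing hospitalization". Section 10 describes the stay as a minimum: "Patients will be at the hospital at least two days after surgery (surgery = day 1").

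**The concern.** The list and its label conflict. If one criterion is enough, an event meeting the sixth is an SAE. If the sixth is optional, the same event may or may not be one, and the text does not say who exercises the option, on what ground, or whether this trial has adopted the criterion at all.

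Judgment about whether an event is medically important is normal and unavoidable. The difficulty here is that, once that judgment has been made, applying the criterion is still left open.

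The classification has consequences. The protocol's text on severity (under the grade Severe) says that seriousness, not severity, guides regulatory reporting obligations. Two investigators could agree that an event was medically important, classify it differently, and both be following the protocol.

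**Working it through.** No arithmetic applies, so the check sets the sections side by side.

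**Step 1: the rule as stated and as labelled.** Take an event that the investigator judges medically important and that meets none of the first five criteria.

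| Reading | Is the event an SAE? |
|---|---|
| Opening sentence: any one criterion suffices | Yes |
| Sixth criterion and explanatory paragraph: optional | Either answer complies |

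Five of the six criteria bind; the sixth does not.

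**Step 2: does any other section make it binding?**
- 9.1.3 defines hospitalization and prolongation and lists exclusions. Its exclusion for emergency or outpatient treatment refers back to the same definition of seriousness, so it settles nothing.
- 9.1.4 and 9.1.5 use the word serious without redefining it.
- The Reporting procedures section provides a yes/no field for seriousness but no rule for completing it.
- 9.1.7 and 9.1.8 start from an event already classed as serious.

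None resolves the conflict.

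**Step 3: what follows from a non-serious entry.**
- 9.1.7 requires a written report only for a serious adverse event.
- 9.1.5 confines SUSARs to reactions that are serious, suspected to be caused by the drug, and unexpected. The commitment that "SUSARs will be reported within 24hours" therefore does not reach an event entered as non-serious.

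**Step 4: what is still captured.** The section Relationship to study drug requires a causality assessment for all adverse events. The Reporting procedures section requires seriousness and expectedness to be entered for each. The three judgments that make up a SUSAR are thus recorded for every event. What is open is the answer to the seriousness question.

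**Step 5: the in-patient setting.** Under section 10, patients stay in hospital from surgery (day 1) for at least two days afterwards. An event in that period cannot cause a new admission, so only the prolongation part of the third criterion is available. An event that is managed during the stay, does not delay discharge, is not life-threatening and leaves no disability can be serious only through the sixth criterion (leaving aside congenital anomaly). After discharge, up to the one-week visit, new hospitalization is available again.

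**The case against.** The strongest reply is one of proportion. This is a single administration of a registered drug already used routinely at the department. Adverse events are asked about daily in hospital and again at one week, and every event receives causality, seriousness and expectedness entries. The investigator remains free to call an important event serious, and the sixth criterion involves case-by-case judgment however it is worded. All of this stands and limits the size of the point. It does not remove the contradiction, because judging whether an event meets a criterion is different from choosing whether the criterion counts.

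A reader might infer more than the text supports:

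- *That such events never enter SUSAR assessment.* They do: all three components are recorded for every adverse event.
- *That angioedema, arrhythmia or convulsions would be missed as SUSARs.* Section 9.1.1 lists these as known side effects, so they are unlikely to count as unexpected. They could illustrate a missed SAE, but probably not a missed SUSAR.
- *That only prolongation and medical significance can catch a non-fatal, non-disabling event.* The life-threatening criterion is binding and covers events that are survived without disability.
- *That the termination rule in 7.1.7 is weakened.* That rule is a risk-benefit judgment on adverse events and does not refer to SAE classification.
- *That prolongation has no baseline.* Section 9.1.3 gives a rule, section 10 a minimum stay, and the severity text an example in which discharge is delayed by a day. An investigator can judge whether an event delayed a given patient's discharge. The stay is stated only as a floor, which is at most a matter for clarification.

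**Conclusion.** The point holds as an internal contradiction in the SAE definition. The protocol permits an event judged medically important to be left non-serious when no other criterion is met, and so to fall outside SAE reports and the SUSAR definition.

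The consequence is possible under-classification at the investigator's discretion. The protocol gives no event rates, so the number of events affected cannot be estimated. The wording applies to every participant, with somewhat more weight during the post-operative stay. The perilymph and blood concentration analysis is not affected.

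The conclusion assumes that the optional labels mean what they say. They may be an unresolved template prompt, but the protocol does not say so, and as written they govern. It is a modest correction to safety reporting that should be made because it is specific and nearly free.

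**What to change.** In the section on Serious Adverse Events:

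1. Delete the word Optional, with its colon, from the sixth criterion.
2. Delete the bracketed repetition in the explanatory paragraph.
3. In that paragraph, replace the permissive verb so that important medical events *are to be classified as SAEs*. Deleting the two labels alone would leave the paragraph discretionary.
4. Confine medical judgment and the individual case decision to whether an event meets the criterion.

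If wished, 9.1.3 can also say against what an additional night is judged, since section 10 gives only a minimum stay. This is a clarification, and no new CRF field is needed.

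The cost is a few words in one section and possibly a few more SAE reports.

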### 9.1.3 Hospitalization – Prolongation of existing hospitalization

Hospitalization is defined as an overnight stay in a hospital unit and/or emergency room.

An additional overnight stay defines a prolongation of existing hospitalization.

The following is not considered an SAE and should be reported as an AE only:

- Treatment on an emergency or outsubject basis for an event not fulfilling the definition of seriousness given above and not resulting in hospitalization.

The following reasons for hospitalizations are not considered AEs, and therefore not SAEs:

- Hospitalizations for cosmetic elective surgery, social and/or convenience reasons.
- Elective treatment of a pre-existing disease or medical condition that did not worsen, e.g., hospitalization for chemotherapy for cancer, elective hip replacement for arthritis.

### 9.1.4 SAEs related to investigational drug

Such SAEs are defined as SAEs that appear to have a reasonable possibility of causal relationship.

### 9.1.5 Suspected unexpected serious adverse reactions (SUSARs)

SUSARs are all serious adverse reactions with **suspected** causal relationship to the study drug that is **unexpected** (not previously described in the Summary of Product Characteristics or Investigator's brochure) and serious. SUSARs will be reported within 24hours.

### 9.1.6 Pregnancy

Any pregnancy that occurs during study participation must be reported to the Investigator/sponsor. To ensure subject safety, each pregnancy must be reported to the Sponsor immediately. The pregnancy must be followed up to determine outcome (including premature termination) and status of mother and child. Pregnancy complications and

elective terminations for medical reasons must be reported as an AE or SAE. Spontaneous abortions must be reported as an SAE.

Any SAE occurring in association with a pregnancy brought to the Investigator's attention after the subject has completed the study and considered by the Investigator as possibly related to the investigational product, must be promptly reported to the Investigator/sponsor. In addition, the Investigator must attempt to collect pregnancy information on any female partners of male study subjects who become pregnant while the subject is enrolled in the study. Pregnancy information must be reported to the Investigator/sponsor as described above.

### **Severity of adverse events**

The severity of clinical AEs is graded on a three-point scale: mild, moderate, severe, and reported on specific AE pages of the CRF.

If the severity of an AE worsens during study drug administration, only the worst intensity should be reported on the AE page. If the AE lessens in intensity, no change in the severity is required.

If an AE occurs during a washout or placebo run-in phase and afterwards worsens during the treatment phase, a new AE page must be filled in with the intensity observed during study drug administration.

#### **Mild**

Event may be noticeable to subject; does not influence daily activities; the AE resolves spontaneously or may require minimal therapeutic intervention;

#### **Moderate**

Event may make subject uncomfortable; performance of daily activities may be influenced; intervention may be needed; the AE produces no sequelae.

#### **Severe**

Event may cause noticeable discomfort; usually interferes with daily activities; subject may not be able to continue in the study; the AE produces sequelae, which require prolonged therapeutic intervention.

A mild, moderate or severe AE may or may not be serious. These terms are used to describe the intensity of a specific event (as in mild, moderate, or severe myocardial infarction).

However, a severe event may be of relatively minor medical significance (such as severe headache) and is not necessarily serious. For example, nausea lasting several hours may be rated as severe, but may not be clinically serious. Fever of 39°C that is not considered severe may become serious if it prolongs hospital discharge by a day. Seriousness rather than severity serves as a guide for defining regulatory reporting obligations.

### **Relationship to study drug**

For all AEs, the Investigator will assess the causal relationship between the study drug and the AE using his/her clinical expertise and judgment according to the following algorithm that best fits the circumstances of the AE:

#### **Not related**

- May or may not follow a temporal sequence from administration of the study product
- Is biologically implausible and does not follow known response pattern to the suspect study drug (if response pattern is previously known).
- Can be explained by the known characteristics of the subject's clinical state or other modes of therapy administered to the subject.

#### **Unlikely**

- There is a reasonable temporal relation between the AE and the intake of the study medication, but there is a plausible other explanation for the occurrence of the AE.

#### **Possibly**

- The AE has a reasonable temporal relationship with drug administration.
- The AE may equally be explained by the study subject's Clinically state, environmental or toxic factors, or concomitant therapy administered to the study subject.
- The relationship between study drug and AE may also be pharmacologically or clinically plausible.

#### **Probably**

- There is a reasonable temporal relation between the AE and the intake of the study medication, and plausible reasons point to a causal relation with the study medication.

#### **Related**

- Reasonable temporal relation between the AE and the intake of the study medication and
- there is no other explanation for the AE and
- subsidence or disappearance of the AE on withdrawal of the study medication and
- recurrence of the symptoms on restart at previous dose (only applies for re-institution of medication).

#### **Not assessable**

- The causal relationship between the study drug and the AE cannot be judged.

#### **Reporting procedures**

A special section is designated to adverse events in the case report form. The following details must thereby be entered:

- Type of adverse event
- Start (date and time)
- End (date and time)
- Severity (mild, moderate, severe)
- Serious (no / yes)
- Unexpected (no / yes)
- Outcome (resolved, resolving, not resolved, resolved with sequelae, unknown, fatal)
- Relation to study drug (Related/ Probably/ Possibly/ Unlikely/ Not related/ Not assessable)

Adverse events are to be documented in the case report form in accordance with the above-mentioned criteria.

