### **7.1.7 Premature termination of the study**

The sponsor has the right to close this study at any time. The IEC and the competent regulatory authority must be informed within 15 days of early termination.

The trial or single dose steps will be terminated prematurely in the following cases:

- If adverse events occur which are so serious that the risk-benefit ratio is not acceptable.
- If the number of dropouts is so high that proper completion of the trial cannot realistically be expected.

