### **8.1.1 Dosage and administration**

Dose: 1mL of Volon® A 10mg or 40mg

Route of administration: intratympanic

Duration: single administration

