## **8.4 Benefit and risk assessment**

This study consists of a perilymph and a blood sample during cochlear implantation. Patients included in the study are deaf or profoundly hearing impaired. As previously shown in other studies sampling of the perilymph is a safe method.

This study can give us information on the absorption of Triamcinolone acetate by perilymph as well as information on the stability of Triamcinolone acetate after absorption of the perilymph. Since Triamcinolone acetate is used in the treatment of sudden SNHL and preoperatively, this study can deliver necessary information on the best timing of drug application and the necessary dose.

Additionally, a blood sample is taken, which can lead to known risks such as infections and hematoma.

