### **9.1.2 Definition of adverse events**

An AE is any untoward adverse change from the subject's baseline condition, i.e., any unfavorable and unintended sign including an abnormal laboratory finding, symptom or disease which is considered to be clinically relevant by the physician that occurs during the course of the study, whether or not considered related to the study drug.

Adverse events include:

- Exacerbation of a pre-existing disease.
- Increase in frequency or intensity of a pre-existing episodic disease or medical condition.
- Disease or medical condition detected or diagnosed after study drug administration even though it may have been present prior to the start of the study.
- Continuous persistent disease or symptoms present at baseline that worsen following the start of the study.
- Lack of efficacy in the acute treatment of a life-threatening disease.
- Events considered by the Investigator to be related to study-mandated procedures.
- Abnormal assessments, e.g., ECG and physical examination findings, must be reported as AEs if they represent a clinically significant finding that was not present at baseline or worsened during the course of the study.

- Laboratory test abnormalities must be reported as AEs if they represent a clinically significant finding, symptomatic or not, which was not present at baseline or worsened during the course of the study or led to dose reduction, interruption or permanent discontinuation of study drug.

Adverse events do not include:

- Pre-planned interventions or occurrence of endpoints specified in the study protocol are not considered AE's, if not defined otherwise (eg.as a result of overdose)
- Medical or surgical procedure, e.g., surgery, endoscopy, tooth extraction, transfusion. However, the event leading to the procedure is an AE. If this event is serious, the procedure must be described in the SAE narrative.
- Pre-existing disease or medical condition that does not worsen.
- Situations in which an adverse change did not occur, e.g., hospitalizations for cosmetic elective surgery or for social and/or convenience reasons.
- Overdose of either study drug or concomitant medication without any signs or symptoms. However, overdose must be mentioned in the Study Drug Log.

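### The AE form records causality against the drug only, so attribution to study sampling is lost; and after a single dose, a drug-caused AE that does not resolve cannot be graded Related

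*Protocol*

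**What the plan says.** All references are to the Protocol.

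- **What the study adds.** Section 8.4: "This study consists of a perilymph and a blood sample during cochlear implantation". Section 7.1.6, on patients withdrawn from the study, presents intratympanic triamcinolone as routine and limits the study to determining concentrations in perilymph and blood.
- **What counts as an AE.** The list in section 9.1.2 includes "Events considered by the Investigator to be related to study-mandated procedures".
- **What is assessed.** Under Relationship to study drug, "the Investigator will assess the causal relationship between the study drug and the AE", on a scale of six grades.
- **What is recorded.** Under Reporting procedures, the required CRF entries contain one causality item: "Relation to study drug (Related/ Probably/ Possibly/ Unlikely/ Not related/ Not assessable". The minimum SAE report in section 9.1.7 names the suspected product and has no item for a suspected procedure.
- **The top grade.** Related joins its criteria with 'and'. The third is "subsidence or disappearance of the AE on withdrawal of the study medication and". The fourth, recurrence on restart, is limited to cases where medication is given again. Section 8.1.1 states "Duration: single administration".

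**The concern.** The AE definition asks the investigator to judge whether an event is related to a study procedure, but the form has nowhere to put the answer. By the protocol's own account, sampling is what the study adds to usual care. Section 8.4 asserts that perilymph sampling is safe and names risks only for the blood draw. Because every patient has implant surgery in the same session, the type, timing, severity and outcome of an event do not by themselves separate an effect of aspiration from an ordinary surgical complication. The investigator's opinion is the only information on that distinction, and it is not kept.

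The second problem lies on the drug scale. A criterion suited to continuing treatment is applied without exemption to one injection of a crystal suspension with a presumed depot effect. The drug-caused events shut out of the top grade are those that do not resolve.

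**Working it through.** No arithmetic applies, since the point depends on no rate, effect size or sample size. The check sets the sections side by side.

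**1. Definition against form.** Section 9.1.2 brings procedure-related events into the AE definition. The causality algorithm addresses the drug only, the CRF list has one causality item out of one for the drug and none for a procedure, and section 9.1.7 names only the product. So the event is recorded and its attribution to sampling is not. The protocol fixes these CRF items itself, so this is not a detail left to an analysis plan.

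**2. Where a sampling-related event would fall.** Assume an event that the investigator attributes to the perilymph aspiration. Section 7 puts sampling 1 to 2 or 20 to 24 hours after dosing, so the timing relative to the drug is usually reasonable as well.

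- *Not related* is possible if the event is implausible for the drug. Its clause on other explanations covers the clinical state and "other modes of therapy administered to the subject", which does not clearly describe a research aspiration.
- *Unlikely* needs reasonable timing and another plausible explanation. It fits at least as well.
- *Possibly* is open if the drug is also a plausible cause. Vertigo, for example, is among the known drug effects in section 9.1.1.
- *Not assessable* is open if the cause cannot be judged.

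Four of the six grades are therefore open to the same event, and none of them names sampling.

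**3. Can attribution be rebuilt from other fields?** The CRF holds type, start, end, severity, seriousness, expectedness and outcome. Section 8 takes perilymph after the cochlea has been opened for the implant, and no group goes unsampled, so there is no internal comparison. The synopsis also lists a Group 5 with RWM, SCC and CSF sampling. More than one sampling site makes a procedure item more useful.

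**4. The grade Related.**

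| Criterion | Single dose, AE resolves | Single dose, AE does not resolve |
|---|---|---|
| Reasonable timing | can be met | can be met |
| No other explanation | can be met | can be met |
| Subsides on withdrawal | met only if later resolution is read as subsidence | cannot be met |
| Recurs on restart | waived | waived |

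The CRF outcome list expects events that are not resolved or fatal. For these the third criterion fails on the text as written.

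**5. Does anything else depend on that grade?** Probably and Possibly need no withdrawal criterion. Section 9.1.4 defines drug-related SAEs by a reasonable possibility of causation, and section 9.1.5 needs only suspicion for a SUSAR. No reporting duty turns on Related.

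**The case against.** The strongest reply is that no events are lost. They are AEs by definition, asked for daily in hospital and again at one week, and described in the SAE report, whose listed content is only a minimum. The algorithm appeals to clinical judgement and best fit, so it need not be read as a checklist. Safety endpoints are marked not applicable in the synopsis. A procedure field would hold opinion, since aspiration and surgery coincide in every patient. This largely stands, and it limits the point to attribution and to one criterion. It does not supply the missing field, and best fit does not make a persistent event one that has subsided.

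Four stronger readings are tempting, and the documents do not support them:

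- *Sampling harm is filed as Not related.* Other grades fit as well or better.
- *No event can ever be Related.* An investigator may count resolution after the single dose as subsidence. The exclusion is firm only for events that do not resolve.
- *The termination rule ignores sampling harm.* Section 7.1.7 reads "If adverse events occur which are so serious that the risk-benefit ratio is not acceptable" and is not confined to drug-related events.
- *The defect can be sized by the zero-event bound for 40 patients*, 1 − 0.05^(1/40) = 0.072, or 7.2%. That bound reflects sample size. If no events of a given type occur, it holds whatever field is on the form.

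Nor is the drug purely background care. Dose and timing are assigned by the study and the use is off-label, so the drug item must stay.

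**Conclusion.** The point holds in two limited parts. First, the protocol makes procedure-related events AEs but provides no place to record relation to sampling, which is the intervention it says the study adds. What is lost is the investigator's attribution, for every sampled patient with such an event; the event itself is kept. Second, on a literal reading of criteria joined by 'and', a drug-caused AE that does not resolve cannot be graded Related after a single administration. The consequence is small, because lower grades still record a causal relation and expedited reporting uses other definitions. Sample size, power and the primary analysis are unaffected. Both parts assume that the CRF follows the list in the protocol and carries no further causality item. The change is worth making because it is nearly free and improves the safety data on sampling.

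**What to change.** 1. Add to the AE page and to the minimum SAE report an item for relation to study procedure (perilymph or other study sampling, study blood draw). Keep it separate from relation to implant surgery, and retain the existing drug item.
2. In the definition of Related, apply the withdrawal criterion only where applicable, as is already done for rechallenge.
3. Leave section 7.1.7 unchanged.

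The cost is one or two fields on a paper CRF and one sentence in section 9, with no new visit or measurement. The limitation is that separating aspiration from surgery will rest on investigator judgement, because every patient has both. The report should say so when it presents the new item.
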